## Abstract

**Background:**

Treatment options for Visceral Leishmaniasis (VL) in East Africa are far from satisfactory due to cost, toxicity, prolonged treatment duration or emergence of parasite resistance. Hence there is a need to explore alternative treatment protocols such as miltefosine alone or in combinations including miltefosine, sodium stibogluconate (SSG) or liposomal amphotericin B. The aim of this trial is to identify regimen(s) which are sufficiently promising for future trials in East Africa.

**Methods/Design:**

A phase II randomized, parallel arm, open-labelled trial is being conducted to assess the efficacy of each of the three regimens: liposomal amphotericin B with SSG, Liposomal amphotericin B with miltefosine and miltefosine alone. The primary endpoint is cure at day 28 with secondary endpoint at day 210 (6 months). Initial cure is a single composite measure based on parasitologic evaluation (bone marrow, spleen or lymph node aspirate) and clinical assessment. Repeated interim analyses have been planned after recruitment of 15 patients in each arm with a maximum sample size of 63 for each. These will follow group-sequential methods (the triangular test) to identify when a regimen is inadequate (<75% efficacy) or adequate (>90% efficacy). We describe a method to ensure consistency of the sequential analysis of day 28 cure with the non-sequential analysis of day 210 cure.

**Discussion:**

A regimen with adequate efficacy would be a candidate for treatment of VL with reasonable costs. The design allows repeated testing throughout the trial recruitment period while maintaining good statistical properties (Type I & II error rates) and reducing the expected sample sizes.

**Trial Registration:**

ClinicalTrials.gov: NCT01067443

## Background

Visceral leishmaniasis (VL), or kala-azar, is the most serious of all Leishmania infections and is fatal if left untreated [1]. A complication of VL, particularly in Sudan, is post kala-azar dermal leishmaniasis (PKDL) where patients have no detectable parasites in the spleen, bone marrow or lymph nodes but develop macular and papulomacular skin lesions in which leishmania parasites may be detected. The median time to occurrence of PKDL is 6 months after treatment [2].

The monotherapeutic treatment options available in East Africa are far from satisfactory due to cost (Liposomal amphotericin B^®^), toxicity (sodium stibogluconate, SSG) or prolonged treatment duration (one month, SSG), resulting in the additional concern of compliance and possible emergence of parasite resistance. Paramomycin, both in monotherapy and in combination with SSG has just recently completed development in the East Africa. However its use in monotherapy does not appear realistic in the region [3,4]. This calls for exploration of new treatment options including miltefosine monotherapy and alternative combination treatment algorithms combining drugs with different modes of action like SSG, Liposomal amphotericin B^® ^and miltefosine which could provide new treatment option with reasonable costs due to reduction in needed dosages and treatment duration and less risk of resistance emerging [5].

Sodium stibogluconate for 30 days is currently the mainstay of VL treatment in East Africa. Liposomal amphotericin B^® ^has also been used in the field, but primarily as a rescue treatment for VL. There is limited experience of the use of miltefosine which is not registered in the region: data are available from only one study, conducted in Ethiopia, which demonstrated efficacy of 93% for miltefosine monotherapy at 6 months follow-up in HIV negative patients [6]. All three drugs have been studied and are registered in India and a phase IV study for miltefosine (28 day course) has been completed [7,8]. In addition a phase-III study conducted in India evaluated 3 short course combinations, including Ambisome plus miltefosine for 7 days, which had a 6 month efficacy of 97% [9].

This study intends to look at potential feasible short course combination therapies as well as evaluate and possibly register miltefosine in its conventional dose and regimen for VL in Sudan and Kenya. It is also intended to supply miltefosine pharmacokinetics in VL patients in East Africa, including children, for whom there is little such information globally. It is a phase-II proof of concept study for efficacy and safety of two potential combinations.

## Methods/Design

### Study Design

A phase II open-label randomized controlled clinical trial.

### Main Objectives

To assess the efficacy of the following treatments for primary VL at day 28:

• the combination of single dose Liposomal amphotericin B^® ^and a 10 day course of SSG

• the combination of single dose Liposomal amphotericin B^® ^and a 10 day course of Miltefosine

• a 28 day course of Miltefosine

### Setting

The areas of the two trial sites are endemic for VL. They are Dooka Hospital, Gedarif State, Sudan and Kimalel Hospital, Baringo district, Kenya. Addition of another Sudanese site will be considered. Data are brought to the Data Centre based at the study's Coordination Centre in Nairobi, Kenya. The trial is being conducted by the Leishmania East Africa Platform (LEAP: http://www.dndi.org/leap-platform) in collaboration with the trial sites and is sponsored by the Drugs for Neglected Diseases *initiative *(http://www.dndi.org).

### Outcome measures

#### Primary outcome

The primary endpoint is initial cure, assessed at day 28 (figure 1) based on clinical assessment and parasitologic evaluation (bone marrow or lymph node for Sudan and bone marrow or spleen aspirate for Kenya).

**Figure 1 F1:**
[figure not shown]
**Consort Trial Diagram**.

#### Secondary outcomes

• Final cure, defined as the percentage of patients cured at day 210 (6 months follow-up) based on clinical evaluation, with parasitology done only if clinically indicated according to a standardised clinical assessment.

• Adverse events and serious adverse events occurring in the three study arms up to day 60.

• Description of the pharmacodynamic properties of all the three arms.

• Description of the pharmacokinetic properties of Miltefosine alone and in combination with Liposomal amphotericin B^®^.

### Allocation

Randomization sequences were generated, stratified by site in pre-determined block sizes by the Data Centre. Randomization codes have been concealed from investigators at the trial sites using sealed sequentially numbered, opaque envelopes. A copy of the randomization list is securely stored at the Data Centre. The envelopes are numbered sequentially externally. Inside each one there is a randomization sheet with the same sequential number as well as the treatment allocation. These randomization sheets are filed in the source documents which the monitor verifies at each site visit to confirm that only one envelope was opened for each patient to ensure integrity of the randomization process.

### Interventions

Liposomal amphotericin B^® ^is being given as a single dose on day 1 at a dose of 10 mg/kg body weight infused in 5% dextrose running for 1-2 hours.

Miltefosine is being given orally at a dose of 2.5 mg/kg body weight daily, up to a maximum of 150 mg, for 28 days when used alone.

Miltefosine is being given orally at a dose of 2.5 mg/kg body weight daily, up to a maximum of 150 mg, for 10 days starting on day 2 following a single dose of Liposomal amphotericin B^® ^10 mg/kg.

SSG is being given IV/IM at a once daily dose of 20 mg/kg body weight daily for 10 days starting on day 2 following a single dose of Liposomal amphotericin B^®^.

Therefore the dose regimens is as follows

• Liposomal amphotericin B^® ^one dose of 10 mg/kg body weight (IV) on day 1 followed by 10 days of SSG at 20 mg/kg body weight (IV/IM) from days 2-11.

• Liposomal amphotericin B^® ^one dose of 10 mg/kg body weight (IV) on day 1 followed by 10 days of miltefosine at 2.5 mg/kg body weight (oral) from days 2-11.

• Monotherapy course of miltefosine at 2.5 mg/kg body weight (oral) from days 1-28.

All failure with compliance will be documented on the trial medication pages of the CRF.

### Screening

#### Inclusion criteria

Patients with clinical signs of VL (fever for at least 2 weeks and splenomegaly) and diagnosis confirmed by visualization of parasites in tissue samples on microscopy, aged between 7 and 60 years inclusive, signed written informed consent, negative HIV status.

#### Exclusion criteria

Patients who have received any anti-leishmanial drugs in the last 6 months/relapse cases, negative lymph node/bone marrow or spleen smears, severe protein and or caloric malnutrition, previous history of hypersensitivity reaction to SSG or Amphotericin B, suffering from concomitant severe infection such as TB or other serious underlying disease which would preclude evaluation of patients response to study medication, suffering from other conditions associated with splenomegaly such as schistosomiasis, previous history of cardiac arrhythmia or an abnormal ECG, female of child bearing age (pregnant or lactating), haemoglobin <5 mg/dL, WBC <1 × 10^3^/mm^3^, platelets <40,000/mm^3^, abnormal liver function tests (ALT and AST) of more than three times the upper limit of the normal range, serum creatinine outside the normal range for age and gender, major surgical intervention within two weeks prior to enrolment. These tests are standardised but it is not feasible to standardise routine clinical laboratory assessments as different machines and reagents are being used. However both internal and external QC will be carried out at both sites on a regular basis and training offered to site staff at the beginning and during the trial to ensure that the data collected are reliable and comparable.

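### The haemoglobin exclusion limit is printed in a unit that no patient's value can fall below, so read literally it excludes nobody

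*Protocol article*

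**What the plan says.** The Exclusion criteria, under Screening in the Methods/Design section, list the haematology limits in one run. The haemoglobin limit is "haemoglobin <5 mg/dL". Beside it stand a white-cell limit of 1 × 10^3 per mm^3 and the limit "platelets <40,000/mm^3". The liver-enzyme and creatinine limits that follow are set relative to the normal range, so they carry no absolute unit.

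This is the only haemoglobin limit in the article. The Inclusion criteria, the Schedule of Assessments and the section on rescue medication neither restate it in another unit nor add a separate criterion for anaemia. The nearest general clause excludes patients with "other serious underlying disease which would preclude evaluation of patients response to study medication".

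**The concern.** The limit is part of the rule that decides who may be randomised, so it is not background text. Haemoglobin in patients is of the order of grams per decilitre. A limit of a few milligrams per decilitre is therefore one that nobody can fall below, and a criterion that nobody can meet does no work.

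Its purpose is patient safety. The trial admits patients from the age of 7, and the notes to Table 1 put the blood drawn from children in the first month at 41 ml in group 2 and 41.5 ml in group 3. A lower limit on haemoglobin has an evident role in such a trial. The article is also the public statement of eligibility, and its Discussion offers the design for use in later drug development. A reader who reuses the criterion as printed would copy one that has no effect.

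**Working it through.** **Inputs**

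- Printed limit: 5 mg/dL (protocol article, Exclusion criteria).
- Conversion: 1 g/dL = 1,000 mg/dL.
- Haemoglobin in living patients: not given in the article. Assumed here to be about 2 to 15 g/dL, a range wide enough to include very severe anaemia.

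**Step 1. Convert the limit.** 5 mg/dL ÷ 1,000 = 0.005 g/dL, which is 0.05 g/L.

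**Step 2. Compare it with values a patient could have.** The ratio to the limit is (haemoglobin in g/dL × 1,000) ÷ 5.

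| Haemoglobin, g/dL | In mg/dL | Multiple of the printed limit | Excluded as printed? |
|---|---|---|---|
| 2 | 2,000 | 400 | No |
| 3 | 3,000 | 600 | No |
| 4 | 4,000 | 800 | No |
| 5 | 5,000 | 1,000 | No |
| 7 | 7,000 | 1,400 | No |
| 10 | 10,000 | 2,000 | No |
| 15 | 15,000 | 3,000 | No |

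The g/dL column is there for comparison only. It does not suggest where the limit should lie.

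**Step 3. Test the assumption.** The conclusion would change only if a patient could have less than 0.005 g/dL. The assumed lower end of 2 g/dL would have to be too high by a factor of 2 ÷ 0.005 = 400. The exact range therefore does not matter.

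**Step 4. Look for other text that does the same job.** The white-cell and platelet limits are of a size that can occur in patients, but they do not measure anaemia. The clause on serious underlying disease turns on whether response can be evaluated. It is a matter of clinical judgement and sets no laboratory limit. An investigator might use it to exclude a severely anaemic patient, but the text does not require that.

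**The case against.** The strongest reply is that the slip reveals itself. A clinician or laboratory worker would see at once that the unit cannot be meant literally. The article condenses a fuller protocol, and under Training it says that site staff were trained on the study protocol and its procedures. That protocol and the case report form may well carry a different unit. This stands as an argument about consequence: an error is established in the article's text and nowhere else. It does not rescue the text. The article did not leave the limit to another document. It stated the limit, and stated it wrongly.

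A reader might go further and infer that severely anaemic patients were let in, or that the enrolled population differs from the one intended. The article does not support that, because nothing in it shows that the limit was applied literally.

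Two passages might seem to support the stronger reading, and neither does:

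- **Range checks.** The section on data collection and data management describes checks for unusual values when the case report forms are entered centrally. Patient identifiers are assigned at randomisation, so these checks look like data cleaning after enrolment. The section does not say that exclusion limits are programmed.
- **Different machines and reagents.** This remark in the Exclusion criteria concerns standardisation of routine laboratory tests, and quality control and training at both sites follow it directly. It says nothing about whether a wrong unit would spread. Equally, quality control of measurements would not correct a limit that is wrongly written.

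**Conclusion.** The criterion is wrong as written. The printed limit equals 0.005 g/dL, and on the assumed range of 2 to 15 g/dL every patient is at least 400 times above it. Read literally, it excludes none of them, and no other part of the article supplies a working haemoglobin limit.

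The conclusion rests on the unit conversion and on an assumed physiological range that could be far wider without changing the result. The most likely cause is a slip of unit in the article. That it reached the sites, the forms or the database is not shown, and neither is any change in who was enrolled.

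The point concerns eligibility and safety wording only. The maximum of 63 patients per arm, the triangular boundaries and the 5% error rates do not depend on it.

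**What to change.** Reconcile both the unit and the number with the approved protocol, and correct the criterion where the article states it. Then confirm that the eligibility form, and any database check that uses a haemoglobin limit, carry the intended unit. This is a confirmation and does not presume that those documents are wrong. The choice of limit stays with the sponsor and the approved protocol, and none is proposed here.

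The cost is a one-line correction and a short check of the forms. It needs no additional patients and changes no analysis.

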### HIV-status and VCT

All patients are offered counselling and screening for HIV (voluntary counselling and testing programme (VCT). This is done at the same time as consent is obtained for inclusion in the trial. Patients who decline VCT or are found to be HIV positive are not eligible to participate in this trial but receive appropriate treatment, according to national treatment guidelines. Additionally, they are referred onwards for treatment, surveillance and follow up according to the national protocol for HIV positive patients.

### Consent

Standardised consent forms, adapted to the local context and translated into local languages and approved by ethics committees are being used. Signatures or thumbprints are obtained for consent, with witnesses in the latter case (illiterate subjects) for adults. In the case of children, the investigator gets their assent once permission of either the child's parent or guardian has been obtained.

Patients who do not meet inclusion criteria or who do not give consent are offered free treatment outside the trial, according to national treatment guidelines.

### Analysis and sample size

#### Analysis of primary endpoint: cure at day 28

The study is designed and will be analyzed according to group-sequential methods, specifically the triangular test [10-12]. Following the trials main objectives, the aim of the analysis is to efficiently identify a regimen that is a) inadequate, so its development can be discontinued, or b) adequate, so its development can proceed. In these terms, the highest efficacy (i.e. percentage of patients cured as per primary outcome) considered inadequate is set in this trial to be 75% (denoted p_0_), and the lowest efficacy considered adequate as 90% (denoted p_a_). The null and alternative hypotheses are *H*_0_: *p *≤ *p*_0 _and *H*_1_: *p *>*p*_a _respectively.

The triangular stopping boundary, as shown in Figure 2, was defined following Ranque et al [10]. With both type I and type II error rates set at 5% (power 95%), and sequential analysis being done after every 15 patients per arm, the maximum sample size required is 189 (63 per arm). The actual sample size may be less than this, depending on when the actual percentage of patients cured leads to a boundary being crossed. The boundaries were calculated using custom-written functions in the R software [13], having checked that they could reproduce the example in Ranque et al [10].

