**Figure 2 F2:**
[figure not shown]
**Triangular region for study arms**. Showing the boundaries for analyzing the sequential trial using the Triangular test with the following parameters (p_0 _= 0.75, p_a _= 0.9, α = 0.05, β = 0.05, and n = 10). The vertical line at *n *= 30 indicates that, for the PK component of the trial, a minimum of 30 patients per arm will be recruited, unless the lower boundary has been crossed before then.

Each analysis consists of calculating the quantities *V *(proportional to current sample size) and Z (number of observed minus expected treatment successes) and plotting them on Figure 2. Hence, for each arm, a line from the origin is plotted over time. Recruitment in an arm will be stopped when this line crosses either boundary of the triangular region. Crossing the lower or upper boundary means concluding inadequacy or adequacy, respectively. Since the three arms will be assessed separately, it is possible that one of them may be stopped prior to others.

The above procedure is subject to a constraint imposed for the PK component of the trial, which requires at least 30 patients in arms 2 and 3, subject to efficacy not being inadequate. Therefore, if the upper boundary is crossed at *n *= 15 (indicating adequate efficacy) that arm will be continued regardless until *n *= 30. However, if the lower boundary is crossed (indicating inadequate efficacy) at *n *= 15, then it will be stopped.

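### Type I and type II error of 5% each cannot both hold for 75% versus 90% with at most 63 patients per arm; the rebuilt triangular boundaries give about 86% power at 90% efficacy, not 95%

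*Protocol article*

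**What the plan says.** Under the analysis of the primary endpoint (Analysis and sample size), the highest efficacy "considered inadequate is set in this trial to be 75" per cent, and "the lowest efficacy considered adequate as 90" per cent. The method is named: "The study is designed and will be analyzed according to group-sequential methods, specifically the triangular test". The error rates follow, "With both type I and type II error rates set at 5% (power 95" per cent), with "sequential analysis being done after every 15 patients per arm", and from these "the maximum sample size required is 189 (63 per arm").

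The text under Figure 2 describes each look as "calculating the quantities *V *(proportional to current sample size) and Z (number of observed minus expected treatment successes"). Crossing the lower line means inadequate and crossing the upper line means adequate. The Figure 2 legend gives n = 10, where the text gives 15.

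The abstract's discussion says that the design tests repeatedly while "maintaining good statistical properties (Type I & II error rates"). The article reports no exact or simulated error rates. The one check it describes is that the custom R functions reproduced a published example.

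**The concern.** The triangular test is built on a large-sample approximation in which Z is normal with mean θV and variance V. That works well for small θ and large n. Here the odds ratio between 90% and 75% is 3, the maximum n is 63 and the outcome is binary. With Z defined as observed minus expected successes, its true mean gain per patient at 90% efficacy is 0.90 − 0.75 = 0.15. The approximation assumes θ × 0.1875 = 1.0986 × 0.1875 = 0.206. An arm at 90% therefore climbs more slowly than the boundaries assume. Its variance is also smaller than assumed (0.90 × 0.10 = 0.09 per patient against 0.1875), but that offsets the slower climb only in part. Reproducing a published example tests the code, not the error rates at 75% versus 90%.

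What is at stake is the false-negative rate. The trial exists to find regimens worth taking forward, and crossing the lower line stops recruitment to the arm with a conclusion of inadequacy.

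**Working it through.** **Inputs from the article.** p0 = 0.75, pa = 0.90, α = β = 0.05, looks every 15 patients, maximum 63 per arm, Z = S − 0.75n where S is the number cured, and θ on the log-odds scale as defined in the article. **Assumption:** V = n·p0(1 − p0) = 0.1875n. The article says only that V is proportional to n.

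**Step 1: reproduce the 63.**
- θ = ln[0.90 × 0.25 / (0.75 × 0.10)] = ln 3 = 1.0986
- a = (2/θ)·ln(1/(2α)) = (2/1.0986) × ln 10 = 4.192; c = θ/4 = 0.2747
- correction for discrete looks: 0.583 × √(15 × 0.1875) = 0.978, so the intercept is 4.192 − 0.978 = 3.214
- upper line Z = 3.214 + 0.2747V; lower line Z = −3.214 + 0.8240V
- the lines meet at V = 6.428 / 0.5493 = 11.70, so n = 11.70 / 0.1875 = 62.4, rounded up to 63

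The stated maximum is reproduced. Looks every 10 would give 66, and no correction would give 82.

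**Step 2: turn the lines into counts of cures.** Upper: S = 3.214 + 0.8015n. Lower: S = −3.214 + 0.9045n.

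| n | lower line | inadequate if | upper line | adequate if |
|---|---|---|---|---|
| 15 | 10.35 | ≤10 | 15.24 | not reachable |
| 30 | 23.92 | ≤23 | 27.26 | ≥28 |
| 45 | 37.49 | ≤37 | 39.28 | ≥40 |
| 60 | 51.06 | ≤51 | 51.30 | ≥52 |

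Every arm has stopped by n = 60. The upper line cannot be reached at n = 15, so the pharmacokinetic rule of continuing to 30 changes nothing.

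**Step 3: exact binomial recursion over these looks.**
- At p = 0.75: P(adequate) = 3.24%.
- At p = 0.90: P(adequate) = 41.14 + 31.05 + 13.95 = 86.14% (n = 30, 45, 60). P(inadequate) = 1.27 + 1.93 + 5.08 + 5.58 = 13.86% (n = 15, 30, 45, 60). Wrong stops already total 8.3% by n = 45.
- At p = 0.92: P(adequate) = 95.05%.

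**Step 4: other readings, power at 90%.**
- legend's n = 10 with looks every 10 (last look at 66 or 70): 89.2% to 89.9%
- boundaries built for n = 10 but looked at every 15: 88% to 89%
- uncorrected boundaries, looks every 15 (maximum 82 to 90): 90.1% to 90.2%

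**Step 5: a ceiling that does not depend on the rebuild.** Any stopping rule with at most 63 patients can be written as a test on 63 observations, so the Neyman-Pearson test at n = 63 bounds its power.
- ≥54 of 63: type I 2.93%, power 90.52%
- ≥53 of 63: type I 5.84%, power 95.32%
- To use exactly 5%, reject at ≥54 and at S = 53 with probability (5 − 2.93)/(5.84 − 2.93) = 0.711. Power = 90.52 + 0.711 × (95.32 − 90.52) = 93.9%.

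Without randomisation, the best fixed-size test within 63 patients is ≥51 of 60 (type I 4.5%, power 92.7%). The smallest fixed size that meets both 5% limits is 70 (≥59 of 70: type I 4.4%, power 95.6%).

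**The case against.** **The 86% rests on a reconstruction.** Figure 2 is not shown, the scale of V is assumed, no integer cut-offs are printed, and the legend and text disagree on the interval. This stands: 86% is the best-supported value because it goes with the stated 63, and the readings in Step 4 run up to about 90%. None of them comes near 95%, and the 93.9% ceiling needs no reconstruction.

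**A reader might infer that no rule within 63 patients can reach 95% power.** That is too strong. At ≥53 of 63 the power is 95.3%, but the type I error is then 5.8%. The statement holds only together with the article's own 5% type I limit.

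**The rates were set as nominal inputs to a published asymptotic method.** That is fair as a description of how they arose, and the 63 is not an arithmetic slip. But the article prints power 95% as a design property, and the abstract says the error rates are maintained.

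**The harm is limited.** Type I error stays below 5%, so a reader should not infer extra false claims of adequacy. The shortfall closes quickly: power is about 95% at 92% efficacy and 99.6% at 95%. The Background cites six-month efficacies of 93% and 97% for related regimens. Arms 1 and 2 also face a second hurdle, a day-210 point estimate of at least 90%, so the day-28 type II error is not their whole false-negative rate. All of this stands. It narrows the consequence without making the printed figure right.

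**A reader might also infer that the sponsor or the DSMB has relied on the 5% rate.** The section on dissemination of results says only that the DSMB receives the triangular analysis.

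**Conclusion.** The statement is wrong as written. For 75% versus 90%, the combination of 5% type I error, 5% type II error and at most 63 patients per arm is impossible: power is at most 93.9%. On the boundaries that reproduce the stated 63, assuming V = 0.1875n and looks at exactly 15, 30, 45 and 60, type I error is about 3.2% and power about 86%. Under the legend's n = 10 with looks every 10, power is about 89% to 90%. Type II error is thus about 10% to 14%, two to three times the stated 5% (13.9/5 = 2.8; 10.1/5 = 2.0). The error is conservative for false adequacy. It bears on regimens with true efficacy from 90% to about 92%, which the article itself counts as adequate.

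**What to change.** 1. Settle whether the boundaries were built for looks every 10 or every 15, and take the integer cut-offs from the R functions actually used.
2. Compute their exact binomial operating characteristics and put these in place of the 95% power in the primary analysis section. If the rebuild is confirmed, the text would say that the boundaries target nominal 5% error rates, that exact type I error at 75% is about 3%, and that exact power is about 86% at 90% efficacy and 95% at about 92%.
3. Qualify the sentence on error rates in the abstract's discussion in the same way.
4. Give the DSMB the true false-negative rate with the triangular analysis.

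The cost is a short calculation, a change of wording and a less favourable stated power. No patient numbers change.

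An option to consider, not a necessary change: with the same looks, lowering the inadequate cut-off at n = 45 to ≤36 and the adequate cut-off at n = 60 to ≥51 gives type I error 4.97% and power 91.6%. Expected n at 75% and 90% becomes 32.1 and 41.6, against 31.2 and 41.1 now. This does not restore 95%. It leaves almost no margin on type I error. It departs from the triangular boundaries behind the tabulated p-value, point estimate and interval, which would have to be re-derived. It would also alter the decision rule of an open-label trial already under way. Keeping both error rates at 5% would require a maximum above 63; the fixed-size benchmark is 70 per arm.
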